#### General Approach

All available data will be included in data listings and tabulations. Data will be summarized by participant counts and related percentages. In general, categorical data will be presented using counts and percentages, whereas continuous variables will be presented using mean, SD, median, minimum, and maximum values. Counts of observed and missing data will also be reported.

#### Safety Analysis

Device- and procedure-related adverse effects will be tabulated and analyzed.

#### Sample Size

This is a prospective study with up to 100 patient participants determined eligible for an evaluation for ASD and up to 15 ECHO Autism clinicians who conduct assessments.

## Results

Participant recruitment began in April 2022. As of June 2022, a total of 41 participants have been enrolled in the study. Data collection is anticipated to continue through 2022, with the data analysis and publication of findings being planned for 2023.

## Discussion

### Principal Findings

To our knowledge, this collaborative observational study will be the first to evaluate the use of a novel AI-based ASD diagnosis aid as part of a real-world primary care diagnostic pathway. It is anticipated that this study will provide valuable feasibility data regarding device integration into a primary care workflow. The study results may help clarify the length of time between initial clinician concern and diagnosis when an AI-based device is used as part of the evaluation process. The results may also provide insights into device performance outside of a research setting, including the percentage of primary care participants for whom it is able to provide a determinate ASD positive or negative result, and concordance between device output and clinical diagnostic determination. Qualitative user experience measures captured as part of the study are anticipated to shed light on the acceptability of the device to both families and clinicians and may help drive future product improvements.

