#### Device Completion

Once the device is prescribed by the clinician, the study sponsor will release the access code to the study team, who will then email it to the caregiver. The caregiver will download the mobile app to their smartphone and access the app using the code. The caregiver will then complete an 18- or 21-item age-dependent caregiver questionnaire (*device input 1*) and record and upload two 1.5-minute to 5-minute videos of the child on the mobile app. The uploaded videos will be remotely reviewed and scored on a 28- or 33-item video analyst questionnaire (*device input 2*) by a trained video analyst via the video analyst portal*.* The ECHO Autism clinician then has the option to *either* complete the health care provider questionnaire, which is a 13- or 15-item age-dependent questionnaire (*device input 3*), themselves or schedule the participant for a telehealth provider appointment, during which the questionnaire will be completed by the telehealth provider. The device algorithm then analyzes all 3 inputs and produces either a *positive ASD*, *negative ASD*, or *indeterminate/no result* output for the clinician to review.

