#### Visit 2: Diagnostic Results Meeting

After the device output is received, the clinician will synthesize their diagnostic impressions (ie, in-person observation, DSM-5 interview, and questionnaires) and the device output to determine whether the participant meets the criteria for a diagnosis of ASD. The clinician may also request access to view the participant’s videos when making a diagnosis. In cases where the clinician’s judgment conflicts with the device output, the diagnostic determination of the clinician (who remains the decision-maker in the diagnostic process) takes precedence. This is consistent with the device’s FDA market authorization status as a diagnosis aid intended to support health care providers in diagnosing ASD rather than as a stand-alone diagnostic device.

For participants whom the clinician determines as meeting the criteria of ASD, the clinician will deliver the diagnosis to the caregiver during visit 2. In addition, the clinician will schedule a 3-month follow-up visit. The research team will then send electronic postdiagnostic questionnaires to the caregiver and the clinician to be completed 1 to 3 (up to 10) days after visit 2.

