**Data collected for secondary objectives**
Patient outcomes correlating with time to initiating therapy following a positive autism spectrum disorder (ASD) diagnosisDistance from patient home to nearest ASD specialist centerLevel of clinician self-efficacy in using the device as part of the evaluation and diagnosis of children with suspected ASDQualitative data on the following: caregiver satisfaction with the diagnostic process; time from caregiver concern to diagnosis; clinician certainty rating for diagnostic determination; clinician satisfaction with using the device as part of the Extension for Community Health Outcomes (ECHO) Autism diagnostic process; caregiver perception of the device with validated questionnaire; determination of whether the use of the device enhances the efficiency and feasibility of the ECHO Autism Communities diagnostic process; likelihood to recommend (clinician and caregiver); efficiency and feasibility of ECHO Autism Community–based diagnostic process, as measured by self-efficacy, certainty ratings, perceived barriers, and practice patterns questionnaires; percentage of positive outcomes correlating with shorter durations between diagnosis and treatment; percentage of caregivers who feel they received a high-quality evaluation; percentage of clinicians with increased self-efficacy in using the device as part of the diagnostic process; percentage of clinicians finding the device helpful in the diagnostic process; percentage of positive device perceptions from caregiver; barriers to app use for caregivers; clinician-perceived barriers to practice implementation of deviceAssessment of insurance coverage or reimbursement (although insurance will not be billed for this study)Amount of time required for clinicians to make a diagnosisPercentage of clinician participants reporting a positive change in practice flow because of using the device as part of their diagnostic processPercentage of patients for whom the device can provide a determinate result (ASD positive or negative)Summary of interventional treatments recommended by the clinician following diagnosisChanges in clinician clinical practice flowChange in quality of life measuresTime associated with device use

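### Agreement between device and clinician is offered as insight into device performance, but the diagnosis already takes the device output into account, so the figure is not independent and is expected to be biased upward by an unknown amount

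*Protocol article*

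**What the plan says.** In the Discussion (Principal Findings), a sentence that begins "The results may also provide insights into device performance outside of a research setting" names two such insights: the share of children with a determinate result, and "concordance between device output and clinical diagnostic determination".

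Visit 2: Diagnostic Results Meeting fixes how that determination is reached. Once the output has arrived, "the clinician will synthesize their diagnostic impressions (ie, in-person observation, DSM-5 interview, and questionnaires) and the device output to determine" whether the child meets ASD criteria. The section adds: "The clinician may also request access to view the participant’s videos when making a diagnosis". It also says that the clinician's determination prevails where it conflicts with the output.

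Under Device Completion, the clinician may personally "complete the health care provider questionnaire, which is a 13- or 15-item age-dependent questionnaire" (device input 3) or leave it to a telehealth provider. Study Design has the treating clinician assess all clinical outcomes.

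Textbox 2 lists a "clinician certainty rating for diagnostic determination" without saying when it is taken. Strengths and Limitations covers access to technology, language, selection of families and clinicians, and attrition. It does not mention that the diagnosis depends on the output.

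**The concern.** To say something about how well a device performs, its result has to be compared with a diagnosis reached without it. Here the result under test is one ingredient of its own comparator, which is incorporation bias. The clinician who makes the diagnosis is unblinded, may have supplied part of the algorithm's input, and may have seen the material behind another part.

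High agreement could then mean that the device is accurate, or that clinicians follow it. The final diagnosis alone cannot tell these apart. A reader who takes the figure as real-world device performance may credit the device with agreement that it produced itself.

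The stated objective is feasibility and impact, and no control group is described. A per-child clinician call made before the output would give a direct within-child measure of impact: how often the output changed the diagnosis or the certainty. The article does not describe one.

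**Working it through.** The protocol states no expected agreement and no figure to reproduce. The check has two parts.

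**1. Order of events**

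- Visit 1: observation and DSM-5 interview, to decide whether the child needs further ASD evaluation. Every child who goes on to the device has passed this step, so it is not a provisional ASD / not ASD call.
- Device Completion: caregiver questionnaire, videos, and input 3 from the clinician or a telehealth provider. The output then goes to the clinician.
- Visit 2: the clinician combines their own evidence with the output and makes the diagnosis.
- Textbox 3: the clinician preproject survey covers self-efficacy, perceived barriers and satisfaction, not the individual child. The post-diagnostic questionnaires follow visit 2.

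No described step yields a per-child determination before the output is seen.

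**2. Direction and possible size**

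Let a be agreement on determinate outputs if the clinician decided without the output, and s the share of initial disagreements in which the clinician moves to the device's result. If switching is only toward the device:

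reported agreement = a + (1 − a) × s, so the shift is (1 − a) × s.

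Both a and s are assumed; the document gives neither.

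| a | s = 0.10 | s = 0.25 | s = 0.50 | s = 0.75 |
|---|---|---|---|---|
| 0.60 | 0.64 | 0.70 | 0.80 | 0.90 |
| 0.70 | 0.73 | 0.775 | 0.85 | 0.925 |
| 0.80 | 0.82 | 0.85 | 0.90 | 0.95 |
| 0.90 | 0.91 | 0.925 | 0.95 | 0.975 |

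Example: 0.80 + 0.20 × 0.25 = 0.85, a shift of 5 points. Over the grid the shift runs from 1 point (0.10 × 0.10) to 30 points (0.40 × 0.75).

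The same reported value can arise in different ways. A figure of 0.85 fits a = 0.85 with s = 0, a = 0.80 with s = 0.25, and a = 0.70 with s = 0.50 (0.70 + 0.30 × 0.50). Final diagnoses alone cannot choose between these.

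Switching away from an agreeing output works the other way. If a share r of initial agreements is lost, reported agreement = a(1 − r) + (1 − a)s. With a = 0.80 and r = 0.02, s = 0.25 gives 0.784 + 0.05 = 0.834, and s = 0 gives 0.784. The net bias is negative only when r exceeds (1 − a)s/a, here 0.05/0.80 = 0.0625.

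The formula covers only the effect of seeing the output. The dependence through input 3 and the videos comes on top and is not quantified.

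**Precision.** If the pivotal trial's share of nearly one third (Device Development) carried over to the cap of 100 children, about 32 would have a determinate output. One child who switched would then move the figure by 1/32, or about 3 points. The exact 95% interval around 26/32 is 64% to 93%. That interval is sampling error, not evidence of bias; it shows only that a bias of this order would not stand out.

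**The case against.** The strongest reply is that concordance is not an end point. It is in neither the primary objective nor Textbox 2, and it appears in one Discussion clause hedged with 'may'. The study is noninterventional. Using the output in the diagnosis is how an authorized diagnosis aid is meant to be used, and the article attributes accuracy evidence to a double-blinded pivotal trial. Agreement in routine use is a legitimate thing to describe. All of this stands and limits the weight of the point. It does not justify presenting the figure as device performance.

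Four stronger readings are tempting, and the documents do not support them:

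- *Agreement is inflated by construction.* The Visit 2 section lets the clinician overrule the device, so agreement is not forced and movement in either direction is possible. Upward bias is the expected direction, not a certainty.
- *The study records no clinician impression before the output.* Baseline clinician questionnaires go out around the time of prescription, interim visit forms exist, and the certainty rating is undated. The contents of these forms are not shown. One can say only that no such record is described.
- *Reported concordance will be some particular inflated value.* Both inputs to the formula are assumed, so the table illustrates and does not predict.
- *The main result is compromised.* Time from clinician concern to diagnosis does not use concordance.

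A provisional call is also not a fully independent reference, since the same clinician may have completed input 3. That is correct and has to be stated with the results. It still removes the direct effect of seeing the output.

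**Conclusion.** The point holds in limited form. Two sections of the article, read together, compare the device output with a diagnosis that includes it, offer the result as insight into performance, and do not list the dependence as a limitation. The direction is expected to be upward, provided that moves toward the device outnumber moves away from it. The size is unknown: 5 points at the assumed a = 0.80 and s = 0.25, and more or less under other assumptions.

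An analysis plan cannot mend this afterwards, because an impression not taken before the output is opened cannot be recovered. The consequence is confined to how one descriptive figure is read and to a missed chance to measure impact within the child. It should be changed, but it does not threaten the primary objective.

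**What to change.** 1. For children whose output has not been opened, add two items to the existing clinician form, completed before the output is viewed: a provisional determination (ASD / not ASD / undetermined) and a certainty rating. If the full forms already contain these, state so and fix their timing.
2. Report concordance of determinate outputs with the provisional determination, and the percentage of children whose determination or certainty changed afterwards. Note that the provisional call is still not fully independent where the clinician completed input 3.
3. In Principal Findings, call agreement with the final diagnosis 'agreement in use', not device performance.
4. In Strengths and Limitations, state that the final diagnosis takes account of the output, and that the clinician may also have supplied input 3 and seen the videos.

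Cost: two form items and one extra table. Asking for a commitment before the output is read adds a small step and could slightly influence routine behaviour. Children already past visit 2 cannot supply the data and are reported separately. With 41 enrolled by June 2022 and a cap of 100, at most 100 − 41 = 59 children were still to be enrolled, plus any enrolled child whose output was unopened. If about 32% of those 59 had a determinate output (assumed), that is about 19 children (59 × 0.32 = 18.9), so the concordance estimate would be imprecise. The wording changes in items 3 and 4 need no new data and can be made whatever is decided on the rest.

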### Comparison With Previous Literature

Although to date, no previous AI-based ASD diagnosis aid primary care–focused studies have been conducted, there is literature supporting the feasibility of diagnosing and managing ASD in primary care settings. For example, a recent systematic review focused on training clinicians to diagnose and manage ASD in primary care [44] found that with appropriate training and support, primary care clinicians can render diagnostic decisions that closely align with specialty team assessments. The reviewed studies also reported reduced wait times for diagnosis when a proportion of evaluations were moved to the primary care setting.

### Strengths and Limitations

Despite well-documented bottlenecks in ASD diagnosis and treatment initiation in the United States [11,45], to date, very few diagnostic tools have been designed to enhance primary care diagnostic capacity. The integration of the device into the ECHO Autism primary care diagnostic pathway in this study offers several potential benefits over existing tools [28-30]. As it was designed with primary care use in mind, the device is more time-efficient than existing instruments and does not require specialist training to administer. For example, in the pivotal trial, the total time burden associated with device use was <30 minutes (median time for caregiver questionnaire completion was 4 minutes and 56 seconds; median time for video analyst scoring from the time video review began to submission of scores was 10 minutes and 54 seconds; self-reported time for health care providers to complete their questionnaire was approximately 10 minutes) [39].

The device is also amenable to remote administration. Caregivers will complete their questionnaires and upload videos remotely using an app on their mobile phones. Video analysts will receive inputs and upload questionnaire outputs remotely through an analyst portal. Pivotal trial data showed no evidence of performance degradation in cases where health care providers completed their questionnaires remotely versus in person. Remote administration may support diagnostic access for families residing in rural and remote locations, as well as families without access to transportation. Remote administration is also useful during public health emergencies such as the COVID-19 pandemic.

Compared with other ASD assessment instruments where the child is observed in a clinical setting, the device leverages home videos that provide naturalistic data about the child’s behavior outside of the clinical setting. These data may help to overcome some of the challenges clinicians and caregivers have described capturing typical child behavior within time-limited clinical encounters [46]. For example, in the clinical setting, the child may become overly reactive to changes in the environment or may not display the behaviors of concern they exhibit at home. Without a picture of the child’s typical behavior, it can be challenging for the clinician to make a confident diagnostic assessment.

The device was also trained on a large and diverse data set in terms of race and ethnicity, socioeconomic status, and gender. Although the pivotal trial was not powered for statistical inference on these covariates, our initial analysis indicated no evidence of inconsistent device performance across these variables [39]. This finding is encouraging and points to the potential of the device to address some of the well-documented disparities in current diagnostic approaches whereby girls and African American and Hispanic children are misdiagnosed more often, as well as diagnosed at a later age, on average, than other groups [47,48].

The device itself and the overall study design have several constraints and limitations. Device use requires access to a smartphone and wireless internet, which not all low-income American families have [49]. In addition, the device is only available in English. Thus, many culturally and linguistically diverse potential participants will be excluded from the study. Selection bias may also be a concern in this study. For example, parents with a higher number of concerns about their child’s development may be more motivated to enroll in the study and complete all device inputs than parents with milder concerns. Attrition is another concern in this study as participation involves multiple steps and engagement over a 3-month period. Given the multiple steps involved, it is possible that study completers may end up representing a more motivated cohort than study leavers. The clinicians who will be recruited into the trial may also represent a biased sample, as by enrolling in ECHO training, they have already demonstrated an interest in enhancing their knowledge of developmental disabilities. In addition, owing to the ECHO Autism curriculum training they receive, clinicians may have more experience and background in ASD diagnosis than other primary care clinicians. In other settings, clinicians with less interest in ASD may be less motivated or confident in using the device and may be less willing to diagnose in the primary care setting.

### Future Directions

The study follows participants for a total of 3 months. Additional follow-up studies are recommended to assess the stability of device performance over a longer period. For the purposes of this study, the sponsors will cover the device cost and associated clinician fees. However, if the device were to become a standard tool in primary care settings, it is unknown to what extent insurance companies would accept and reimburse these costs. Questions also remain regarding whether and how families with no health insurance can access the device. We recommend that future device studies be conducted in populations who have not completed the ECHO Autism diagnostic training program. Such research could help answer important questions about the feasibility of device use in primary care clinician populations with less ASD-specific knowledge and training.

### Conclusions

If device integration into primary care practice proves feasible and efficacious, it may support clinicians in diagnosing more children in the primary care setting and reducing current delays between the first ASD concern and eventual diagnosis. Streamlining primary care ASD diagnosis could potentially reduce strain on specialist services by allowing for the diagnosis of less ambiguous cases in primary care and quicker referral of complex cases to relevant specialist teams. Ultimately, we hope that decreasing the time to diagnosis and age of diagnosis through enhanced primary care capacity will allow a greater proportion of children to commence early intervention during a critical neurodevelopmental window.

## Abbreviations

AI: artificial intelligence
ASD: autism spectrum disorder
DSM-5: Diagnostic and Statistical Manual of Mental Disorders–fifth edition
ECHO: Extension for Community Health Outcomes
FDA: Food and Drug Administration
STAT: Screening Tool for Autism in Toddlers and Young Children
